## Abstract

**Background:**

Polymyxin B-immobilized fiber column (PMX; Toraymyxin column) was approved for the relief of systemic inflammatory response syndrome caused by bacterial infection or endotoxemia. PMX reduces lung damage by removing leukocytes and cytokines in addition to endotoxin removal in the setting of idiopathic pulmonary fibrosis. Acute exacerbation of interstitial pneumonia pathologically presents with diffuse alveolar damage (DAD). PMX direct hemoperfusion (PMX-DHP) demonstrated efficacy, improving oxygenation. The SARS-CoV-2 virus causes COVID-19, which emerged in December 2019. The condition may become severe about 1 week after onset, and respiratory failure rapidly develops, requiring intensive care management. A characteristic of COVID-19–related severe pneumonia is ground-glass opacities rapidly progressing in both lungs, which subsequently turn into infiltrative shadows. This condition could be classified as DAD. As for the congealing fibrinogenolysis system, D-dimer, fibrin/fibrinogen degradation product quantity, and prolonged prothrombin time were significant factors in nonsurviving COVID-19 cases, associated with aggravated pneumonia. Clinical trials are being conducted, but except for remdesivir and dexamethasone, no treatments have yet been approved. COVID-19 aggravates with the deterioration of oxygen saturation, decrease in lymphocytes, and the occurrence of an abnormal congealing fibrinogenolysis system, leading to diffuse lung damage. Once the condition transitions from moderate to severe, it is necessary to prevent further exacerbation by providing treatment that will suppress the aforementioned symptoms as soon as possible.

**Objective:**

This study aims to access treatment options to prevent the transition from acute exacerbation of interstitial pneumonia to DAD. The mechanism of action envisioned for PMX-DHP is to reduce congealing fibrinogenolysis system abnormalities and increase oxygenation by removing activated leukocytes and cytokines, which are risk factors for the aggravation of COVID-19–related pneumonia.

**Methods:**

We will conduct a multicenter, prospective, intervention, single-group study to evaluate the efficacy and safety of direct hemoperfusion using PMX-DHP for patients with COVID-19. Efficacy will be evaluated by the primary end point, which is the rate of Ordinal Scale for Clinical Improvement after PMX-DHP of at least 1 point from a status of 4, 5, or 6 on day 15. The effect of PMX-DHP will be estimated by setting a control group with background factors from non–PMX-DHP patients enrolled in the COVID-19 registry. This study will be carried out as a single-group open-label study and will be compared with a historical control. The historical control will be selected from the COVID-19 registry according to age, gender, and severity of pneumonia.

**Results:**

The study period is scheduled from September 28, 2020, through April 30, 2023. Patient enrollment was scheduled from the Japan Registry of Clinical Trials publication for March 31, 2022. Data fixation is scheduled for October 2022, with the publication of the results by March 2023.

**Conclusions:**

From a clinical perspective, PMX-DHP is expected to become an adjunctive therapy to address unmet medical needs and prevent the exacerbation from moderate to severe acute respiratory distress syndrome in COVID-19 cases.

**International Registered Report Identifier (IRRID):**

DERR1-10.2196/37426

## Introduction

Regarding polymyxin B-immobilized column (PMX), Toraymyxin was approved in October 1993 for the relief of systemic inflammatory response syndrome caused by gram-negative bacterial infection or endotoxemia by “selectively adsorbing and removing endotoxin in the blood by whole blood hemoperfusion.” It has been reported to be effective against acute lung injury/acute respiratory distress syndrome caused by sepsis, which is an indicator [1-4]. This is thought to be because PMX reduces lung damage by removing leukocytes and cytokines in addition to endotoxin removal. In terms of treatment results, idiopathic pulmonary fibrosis (IPF), which has been the subject of previous clinical studies, is the most common idiopathic interstitial pneumonia (accounts for about 50% of idiopathic interstitial pneumonia worldwide) and has a chronic and progressive course. Once advanced fibrosis progresses, irreversible honeycombing occurs, leading to an extremely poor prognosis [5,6]. The total number of Japanese patients with IPF is estimated to be at least around 10,000 [7]. Acute exacerbation of interstitial pneumonia pathologically presents with diffuse alveolar damage (DAD). In recent years, reports on PMX (Toraymyxin by Toray Industries Inc) direct hemoperfusion (PMX-DHP) for this acute exacerbation have mentioned its efficacy, which includes the improvement of oxygenation [8-15]. A study of 73 IPF cases with acute exacerbation has noted the improvement of oxygenation upon carrying out PMX-DHP [14]. Further, an exploratory study on the efficacy and safety of direct hemoperfusions using PMX-DHP for patients with IPF with acute exacerbation was conducted from 2014 to 2019 for the acute exacerbation of IPF. In this study, the survival rate of 20 enrolled cases 4 weeks after PMX-DHP was 65%, which far exceeded the 10% to 40% threshold survival rate in previous reports [15,16] and exceeded the expected upper limit of the survival rate of 60%. Moreover, the result was well above the expected lower limit of the 95% CI, which was 39%.

SARS-CoV-2 was identified as the causative virus of an unknown pneumonia (COVID-19) that emerged in Wuhan City, Hubei Province, China in December 2019. Depending on the case, the condition become severe about 1 week after onset, and respiratory failure rapidly develops, requiring intensive care management [17]. Patients may have markedly impaired oxygenation early in the course of the disease, which is said to be due to increased activity of the coagulation system; plasminogen activator inhibitor-1 expression is increased in older adults and in people with hypertension, obesity, and diabetes, which are risk factors for COVID-19; and in severe cases of COVID-19, STAT3 and plasminogen activator inhibitor-1 activation is escalated, leading to catastrophic consequences. A characteristic of COVID-19–related severe pneumonia cases is ground-glass opacities rapidly progressing in both lungs visible in chest computed tomography findings [18]. With subsequent progression toward severity, these opacities turn into infiltrative shadows [19]. This condition could be classified as DAD [20]. According to the analysis results of 191 COVID-19 cases in Wuhan, 100% of nonsurviving cases have sepsis while 93% have acute respiratory distress syndrome. The three most relevant risk factors in the early stage were age, Sequential Organ Failure Assessment score, and 1 μg/mL or higher D-dimer [21]. As for the congealing fibrinogenolysis system, according to a different report, D-dimer, fibrin and fibrinogen degradation product, and prolonged prothrombin time were significant factors in nonsurviving COVID-19 cases, suggesting that the effects of the congealing fibrinogenolysis system are associated with the aggravation of pneumonia [22]. As of February 2021, clinical trials and clinical studies are being conducted with several existing treatments, but except for remdesivir and dexamethasone, no drugs or treatments have yet been approved by the Japanese regulatory authorities.

As previously mentioned regarding the clinical significance of PMX-DHP, we believe that COVID-19 aggravates with the rapid deterioration of oxygen saturation, decrease in lymphocytes, and the occurrence of an abnormal congealing fibrinogenolysis system, leading to complex diffuse lung damage. Virus growth suppression caused by antiviral action can be expected if the initial growth rate is suppressed; however, once the condition transitions from moderate to severe, it is most necessary to address unmet medical needs to prevent further exacerbation by providing treatment that will suppress the aforementioned symptoms as soon as possible and prevent the transition to DAD. Simply put, we believe that, in addition to antiviral drugs, it is most necessary to acquire treatment options to prevent progression from rapidly worsening interstitial pneumonia to DAD. The complex mechanism of action envisioned for PMX-DHP is to reduce congealing fibrinogenolysis system abnormalities and increase oxygenation by removing activated leukocytes and cytokines, which are risk factors for the aggravation of COVID-19–related pneumonia. Therefore, from a clinical perspective, PMX-DHP is expected to become an adjunctive therapy to address unmet medical needs and prevent the progression from moderate to severe condition. The scientific rationale of this study is to carry out PMX-DHP, in addition to regular medical care, for patients with COVID-19 and to aggregate and analyze the acquired information. This study will help determine PMX-DHP treatment options in the medical setting by quickly collecting and publishing information on patient background and on the efficacy and safety of treatment by PMX-DHP.

## Methods

### Study Design

We will conduct a multicenter, prospective, intervention, single-group study to evaluate the efficacy and safety of direct hemoperfusion using PMX-DHP for patients with COVID-19. Efficacy will be evaluated by the primary end point, which is the rate of Ordinal Scale for Clinical Improvement after PMX-DHP of at least 1 point from a status of 4, 5, or 6 on day 15, based on previous studies for COVID-19 treatment (Table 1) [23]. Further, safety will be confirmed by the incidence of serious adverse events and problems. The effect of PMX-DHP will be estimated by setting a control group with background factors from non–PMX-DHP patients enrolled in the COVID-19 registry at participating facilities. Since this study will carry out PMX-DHP, setting up a sham group is difficult in terms of ethics because the therapy is relatively invasive. As such, this study will be carried out as a single-group open-label study and will be compared with a historical control. The historical control will be selected from the COVID-19 registry according to age, gender, and severity of pneumonia.

**Table 1 table1:** Purpose and end points.

Purpose			End points		Validity and reason for selection of end points
**Primary**					
	To evaluate the efficacy of PMX-DHP^a^	Improvement rate (decrease) of 1 point or more from status 4, 5, or 6 on day 15 based on the eight-category evaluation		Because it was the primary end point in previous studies for COVID-19 treatment	
**Secondary**					
	To evaluate the efficacy and safety of PMX-DHP	Pathological improvement rate (status 1, 2, and 3 in the aforementioned eight categories) from the start of PMX^b^. PaO2/FiO2 improvement on day 4 and day 8 Changes in cytokines, coagulation markers, and urinary biomarkers Occurrence of serious adverse events and problems Invasive mechanical ventilation avoidance rate and duration of use ECMO^c^ avoidance rate and duration of use Mortality rate		Evaluation of respiratory function, safety, and efficacy of PMX-DHP	

^a^PMX-DHP: polymyxin B-immobilized fiber column direct hemoperfusion.

^b^PMX: polymyxin B-immobilized fiber column.

^c^ECMO: extracorporeal membrane oxygenation.

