### Eligibility Criteria and Recruitment

All of the following inclusion criteria must be met to participate in this study: dyspnea unexplainable by other diseases (heart failure, renal failure, etc), diagnosis with SARS-CoV-2 infection through polymerase chain reaction or loop-mediated isothermal amplification within 1 week, at least one lung opacity on imaging suggestive of consolidation, P/F ratio of 300 or below or an SpO2 of 93% or below (indoor air), being hospitalized, requiring supplemental oxygen, requiring nasal high-flow oxygen therapy or noninvasive mechanical ventilation or requiring invasive mechanical ventilation, 16 years or older at the time of consent, and written consent. Consent is obtained from patients with pneumonia who are hospitalized for COVID-19 and who may meet the eligibility criteria.

Consent is obtained in writing from the individual. Informed consent will be obtained from a representative of the patient if the patient is a minor or objectively judged to have insufficient understanding of the subject due to a serious illness. The representative will be selected from the patient’s spouse, parents, siblings, children/grandchildren, grandparents, relatives living in the same household, or close relatives of the patient.

The following tests, observations, and evaluation will be performed as part of the screening test: vital information (date of birth, gender, height, weight, presence of oxygen therapy); clinical history (onset: date of onset, symptoms), treatment history (type, treatment period of therapeutic drugs/therapy), medical history, complications, allergies, date of admission, date of polymerase chain reaction positive result, concomitant drug confirmation (medication currently being taken by the patient shall be confirmed at the time of the screening), vital signs, blood test (hematological test, blood biochemical test), urinalysis, and imaging test (presence of pneumonia complications).

As a result of the screening, if the patient meets the enrollment criteria stated in the eligibility criteria, they will be enrolled to the study, and PMX-DHP will commence. Otherwise, the patient fails the screening and will no longer participate in the study.

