### Statistical Analysis

The main purpose of this study is to verify the efficacy in PMX-DHP cases compared to the control in the COVID-19 registry for the primary end point. Particularly, the efficacy of PMX-DHP will be evaluated by comparing the improvement rate (decrease) of 1 point or more from status 4, 5, or 6 on day 15 based on the eight-category evaluation with the COVID-19 registry.

Not hospitalized with resumption of normal activitiesNot hospitalized but unable to resume normal activitiesHospitalized not requiring supplemental oxygenHospitalized requiring supplemental oxygenHospitalized requiring nasal high-flow oxygen therapy, noninvasive mechanical ventilation, or bothRequiring invasive mechanical ventilationRequiring ECMODeath

The status and the percentage of PMX-DHP cases at each evaluation time will be calculated, and the number and percentage of people whose day 15 status improved by 1 or more points from day 1 will be calculated. Furthermore, the following analysis will be planned for comparison with control cases.

Bias is included when comparing the rate of improvement of control cases for 15 days from the time of hospitalization against cases that underwent PMX-DHP several days after hospitalization. Therefore, the number of days from hospitalization to the date of PMX-DHP administration will be calculated for each case.

The effect of PMX-DHP will be estimated using the propensity score based on the data, which integrates this study and the registry. The propensity score will be created based on age, gender, body temperature, etc, and analysis methods such as matching will be used. A significance level on both sides of 5% will be used.

The following results will be calculated for cases enrolled in this study:

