Pathological improvement rate on day 15 (status 1, 2, and 3 in the eight categories) from the start of PMX. The number and percentage of people who reached status 1, 2, and 3 on day 15 at a 95% CI will be calculated. Furthermore, the same items will be calculated on day 29.P/F improvement on day 4 and 8. The descriptive statistics of P/F on day 1, day 4, and day 8 will be calculated and presented on a transition chart.Changes in cytokines, coagulation markers, and urinary biomarkers. The descriptive statistics of clinical laboratory test values that take continuous values will be calculated. For laboratory findings, which are classification variables, the number and proportions at each level will be calculated at each point in time.Invasive mechanical ventilation avoidance rate and duration of use. The number and proportion of people who underwent invasive mechanical ventilation between day 15 and 29 will be calculated.ECMO avoidance rate and duration of use. The number and proportion of people who underwent ECMO between day 15 and 29 will be calculated.

Similar to the primary end point, the efficacy of PMX will be evaluated for the aforementioned secondary end points using propensity scores based on data integrated with the enrolled cases in the registry.

The safety end point is the incidence and rate of adverse events. Multiplicity will not be adjusted in the analysis of safety end points. In the estimation of the ratio to the number of cases and presence or absence of occurrence, an exact 95% CI for the binomial distribution will be calculated for each group.

In addition to clinical laboratory items, continuous quantity data will be tabulated by group through descriptive statistics, while classification variables will be tabulated through the number of people or rate, among other appropriate methods.

Furthermore, PMX malfunctions will also be tabulated. Subgroup analysis will be performed by status and age at the time of enrollment.

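### The invasive ventilation avoidance rate is calculated without restricting it to patients off ventilation on day 1, so it mixes avoidance with liberation and moves with the share ventilated at entry

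*Protocol article*

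**What the plan says.** All references are to the protocol article, Methods.

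- **Who enters.** Eligibility Criteria and Recruitment admits patients "requiring nasal high-flow oxygen therapy or noninvasive mechanical ventilation or requiring invasive mechanical ventilation". ECMO is an exclusion criterion; invasive ventilation is not. Table 1 defines the primary end point as "Improvement rate (decrease) of 1 point or more from status 4, 5, or 6 on day 15", and the eight-category list in Statistical Analysis makes status 6 the invasively ventilated category.
- **The end point.** Table 1 lists "Invasive mechanical ventilation avoidance rate and duration of use" among the secondary end points for efficacy and safety.
- **The calculation.** Statistical Analysis introduces the secondary results with "The following results will be calculated for cases enrolled in this study". For this item it states "The number and proportion of people who underwent invasive mechanical ventilation between day 15 and 29 will be calculated". It names no at-risk subset.
- **The comparison.** The same section then evaluates PMX efficacy on these secondary end points against the registry, using propensity scores.
- **Related provisions.** Study Design selects controls by age, gender and severity of pneumonia. Statistical Analysis plans subgroups by status and age at enrolment. The propensity covariates it names are age, gender and body temperature, followed by an open-ended 'etc'.

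**The concern.** A patient at status 4 or 5 on day 1 can avoid invasive ventilation. A patient at status 6 is already on it and can only come off it. A single proportion over both groups answers neither question cleanly. Its value shifts with the proportion of status-6 patients even when PMX does nothing, so a difference in that proportion between PMX and registry patients appears as a difference in avoidance.

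The end point matters because it is close to the stated aim (Abstract, Conclusions; Introduction) of preventing progression from moderate to severe disease. The parallel ECMO end point does not share the problem, because patients on ECMO at entry are excluded. The primary end point is not touched by this point either: a patient at any of the three starting statuses can improve by one point.

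**Working it through.** The article gives no expected value for this end point, so there is no figure of its own to reproduce. Its power figures concern the primary end point and do not bear on this.

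**Inputs, all assumed because the article gives none**
- s: share of patients at status 6 on day 1. Taken as 10% to 50%; 10% in PMX cases and 30% in controls for the comparison.
- q: proportion of status 4 and 5 patients counted as avoiding ventilation. Taken as 80%, with a range of 70% to 90%.
- r: proportion of status-6 patients counted as having avoided ventilation. This depends on the counting rule.

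**Formula.** All-patient rate = (1 - s) x q + s x r. With no PMX effect, q and r are the same in both groups, so the spurious difference = (s in controls - s in PMX) x (q - r).

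**Reading A: ventilation from day 1 counts, so r = 0**
- At q = 80%, s = 10%, 20%, 30% and 50% give 72%, 64%, 56% and 40%. Restricted to status 4 and 5, the rate is 80% at every s.
- s = 10% v 30%: 0.9 x 0.8 = 72% v 0.7 x 0.8 = 56%, a gap of 16 points.
- Over q = 70% to 90%, the gap is 0.2 x 0.7 = 14 to 0.2 x 0.9 = 18 points.
- The rate cannot exceed 1 - s. With the 30 PMX cases used in Sample Size Estimation, 6 ventilated at entry would cap it at 24/30 = 80%.

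**Reading B: the stated window, day 15 to 29**

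A status-6 patient extubated before day 15 and not re-ventilated counts as having avoided ventilation, so r is above 0. Take r = 50%.
- s = 10%: 0.9 x 0.8 + 0.1 x 0.5 = 77%.
- s = 30%: 0.7 x 0.8 + 0.3 x 0.5 = 71%.
- The gap is 6 points, or 0.2 x (0.8 - 0.5).

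Under B the gap vanishes only if r = q, that is, if ventilated patients come off ventilation as often as the others stay off it.

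**Does pooling dilute a true effect?** Take s = 40% in both groups and a true 80% v 60% in status 4 and 5.
- Reading A: 0.6 x 0.8 = 48% v 0.6 x 0.6 = 36%, so 20 points become 12.
- Reading B, if PMX also helps extubation (r = 50% v 30%): 48% + 20% = 68% v 36% + 12% = 48%, which is 20 points again.

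Dilution is therefore possible but depends on r.

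**The case against.** **The denominator may be set elsewhere.** An article condenses a fuller document, and the phrase about enrolled cases may serve only to separate within-trial results from the registry comparison. That is a fair reading, and the full protocol may contain a restriction. But the article is not merely silent: it states a population and a calculation and uses the result for an efficacy comparison. Followed as written, these include status-6 patients.

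**The stated window changes the arithmetic.** This stands. A reader might infer that status-6 patients can no longer succeed on this end point, that the spurious gap is 16 points, and that any true effect must be diluted. All three require ventilation to count from day 1, whereas the only window stated is day 15 to 29. Under that window an early-extubated status-6 patient is a success, the illustrative gap falls to 6 points, and dilution is not certain. The dependence on entry status remains.

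**The plan has safeguards.** Selecting controls by severity of pneumonia may balance ventilation at entry. Subgroups by entry status, if applied to this end point, would separate status 6 from status 4 and 5. Both count in the plan's favour. But severity is not tied to day-1 ventilation, and the named propensity covariates do not include status, so balance is neither assured nor ruled out. Neither safeguard changes the headline rate, and avoidance has no clear meaning in a status-6 subgroup.

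**Duration of use.** A reader might infer that duration mixes ventilation begun before and after day 1. The article does not say when duration starts or in whom it is counted, so this is not established.

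**Conclusion.** The point holds in a limited form. The article admits patients on invasive ventilation and gives an avoidance calculation with no at-risk restriction. The headline rate therefore mixes avoidance with liberation and depends on the status-6 share.

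The size cannot be derived from the article. With 80% avoidance in status 4 and 5, status-6 shares of 10% v 30% and no PMX effect, the spurious gap runs from about 6 points (day 15 to 29 window, half of status 6 off ventilation by then) to 16 points (counting from day 1). If control selection equalises the shares, this gap disappears, although the PMX rate still describes two different populations. The direction of any imbalance is unknown, so the bias could favour either group.

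This affects one secondary end point and is worth correcting because the remedy is simple.

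**What to change.** In Table 1 and Statistical Analysis:

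1. Calculate and compare the avoidance rate only in PMX and registry patients at status 4 or 5 on day 1.
2. Count as avoided only patients alive without invasive ventilation, or report deaths without intubation separately. Otherwise a patient who dies unventilated would count as a success.
3. For patients at status 6 on day 1, report the proportion alive and off invasive ventilation at days 15 and 29 as a separate item.

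The counting window needs its own clarification; correcting it would not repair the denominator.

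**Cost.** This changes analysis wording only, since the primary end point already needs day-1 status. The avoidance rate rests on fewer patients. With 30 PMX cases and a rate of 80%, the approximate 95% half-width is 1.96 x sqrt(0.8 x 0.2 / 30) = 14 points. If 20% are at status 6, 24 patients remain and it becomes 1.96 x sqrt(0.8 x 0.2 / 24) = 16 points. If 40% are, 18 remain and it becomes 1.96 x sqrt(0.8 x 0.2 / 18) = 18 points. The status-6 item would rest on few patients and be descriptive.
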